**Recruitment**			
**% of target number of participants recruited (target: 60; 12 month recruitment period)**	< 70%	70–99%	100%
**Adherence**			
**% of recruited participants who adhere to their allocated intervention**	< 65%	65–84%	85–100%

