### Study population

This trial aims to recruit 60 participants: 30 in the intervention group and 30 in the control group. A formal sample size calculation was not used for this feasibility study; it is anticipated that this sample size will provide sufficient information on the study objectives to inform a future main trial. The inclusion criteria will be adult participants (male or female; aged ≥ 18 years) with a diagnosis of any SMI (schizophrenia, psychosis, bipolar disorder and major depression), not meeting the national physical activity guidelines. A validated questionnaire, the General Practice Physical Activity Questionnaire (GPPAQ), will be used to screen physical activity levels [25]. Exclusion criteria will be those with significant movement impairment, those identified as ‘Active’ using the GPPAQ screening tool and those unable to understand English or who lack comprehension to understand the purpose of the study and give written informed consent. The revised Physical Activity Readiness Questionnaire (PAR-Q) [26] will be used to identify any health-related risks of exercising that would require a participant to consult their general practitioner prior to changing their physical activity levels.

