### Intervention

Participants assigned to the WORtH intervention group will attend an initial educational group session where they will meet their clinician-coach, a clinician from the mental health team who has been trained to deliver the WORtH intervention. The content of the group education session will introduce the benefits of increasing their physical activity and reducing their sedentary behaviour, along with strategies to help them to move more and sit less in their daily routines. During the session, participants will be given a physical activity monitor (Mi Band 3, Xiaomi Corporation, Hong Kong) to self-monitor their daily steps throughout the intervention and an activity diary where they will record their physical activity and sedentary behaviour goals, complete their action plans and self-monitor by recording daily goal attainment.

Participants will be invited to attend a weekly group walk led by a clinician-coach; this will provide an element of social support. Additionally, they will meet with their assigned clinician-coach every 2 weeks. During coaching sessions, the participant will be supported to set move more (physical activity) and sit less (sedentary behaviour) goals which will be reviewed and progressed during the programme. Participants will be supported to complete an action plan of when, where and how they plan to meet their goals including strategies to overcome anticipated barriers discussed during the session.

The Behaviour Change Technique Taxonomy version 1 (BCTTv1) [27] provides a standardised and well-defined taxonomy of active components of behaviour change that can be used in the design and evaluation of interventions [28]. This approach has been used by our team to develop and define a number of physical activity and sedentary behaviour interventions [29–32] and helped to inform the behaviour change techniques (BCTs) to embed within the WORtH intervention to promote increased physical activity and reduced sedentary behaviour in people with SMI. WORtH intervention components were mapped to the BCTTv1 [27] independently by two authors ([name]) to identify the BCTs targeting increased physical activity and reduced sedentary behaviour in people with SMI. A summary of the core BCTs embedded within the WORtH intervention is presented in Fig. 2.

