### Control

Participants assigned to the control group will be invited to attend a single one-to-one information session where they will be given an A5 leaflet briefly outlining the benefits of being more active and reducing sedentary behaviour and advice on how to do so. During the session, the researcher will read through the leaflet with the participant and give them the opportunity to ask questions. The researcher will complete a pro-forma with details of the duration of the session and a checklist of information to be covered in the session. At the end of the session, they will be informed of the date of end of study assessment. Immediately after the session, the researcher will make a handwritten note of the conversation and comments.

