### Implications of COVID-19 on study delivery

This study is being rolled out during the COVID-19 global pandemic. Therefore, current public health restrictions in place relating to COVID-19 will be followed, aiming to reduce in-person contact with participants to reduce the risk of transmission for patients and staff, where possible (Table 2). Recruitment to the study was open both pre- and post-suspension due to COVID-19; as such, participants recruited to the trial pre-suspension were cluster-randomised in a 1:1 ratio and received an in-person intervention, while participants recruited post-suspension are individually randomised in a 2:1 ratio and receive remote delivery of the intervention as outlined in Table 2.

**Table 2 Tab2:** Proposed protocol changes in response to COVID-19

Study activity	Measures taken
Recruitment	Study information will be shared via email, where possible, or post. Screening visit will be completed via telephone. Consent form will be completed and returned by post or email, where possible. Participants can identify a carer to support them. Carer consent will be obtained. Rolling recruitment will take place as there will be no group component to the intervention and to reduce clinician burden when delivering the intervention.
Randomisation	Participants will be randomised at individual level (due to practicalities of rolling recruitment, e.g. to ensure allocation concealment as participants from the same residential setting may enrol at different times) to either intervention or control group in a 2:1 ratio after completion of the baseline assessment. The allocation ratio was changed to ensure sufficient number of participants are exposed to the intervention and optimal information on intervention delivery can be collected, given that there may be recruitment challenges with remote recruitment and delivery. With 2:1 allocation ratio, two-thirds of participants enrolled will be randomised to the intervention group. Allocations will be undertaken using a permuted block design with unequal block sizes (of 3, 6, 9). A researcher independent of the study will generate the randomisation sequence and allocate the participant after baseline data collection. The randomisation sequence will be concealed from members of the research team involved in participant management to prevent biased allocation [47, 48].

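### The adherence row of Table 1 pools both arms, so its colour depends on control attendance and on the allocation ratio as well as on adherence to WORtH

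*Protocol article*

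**What the plan says.** The progression table (Table 1, under Data analysis) has one adherence row: the percentage "of recruited participants who adhere to their allocated intervention". Its Red, Amber and Green bands are below 65%, 65–84% and 85–100%. The denominator is everyone recruited, each person judged against their own arm, and no arm-specific rate enters the rule. The worst of the four elements in the table sets the action.

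The two allocations differ widely in what they ask:

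- Control section: "Participants assigned to the control group will be invited to attend a single one-to-one information session".
- Intervention section: an education session, coaching every two weeks, goals, action plans, and self-monitoring with an activity monitor and diary. In addition, "Participants will be invited to attend a weekly group walk led by a clinician-coach". Table 2 later makes the walk depend on distancing guidance.

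On numbers, the Study population section states: "This trial aims to recruit 60 participants: 30 in the intervention group and 30 in the control group". The COVID-19 section says that "participants recruited to the trial pre-suspension were cluster-randomised in a 1:1 ratio and received an in-person intervention", and that later participants are randomised individually: "With 2:1 allocation ratio, two-thirds of participants enrolled will be randomised to the intervention group".

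Two other places bear on the point. Objective i covers adherence rates in both arms. The Data analysis text describes retention and adherence as the share who complete the intervention, which could be read as WORtH only.

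**The concern.** The stated aim is to test whether the WORtH programme is feasible. Whether people allocated to it keep to it is the adherence question that bears on a main trial. Attending a single session is a much lighter requirement, yet each control participant counts as much as each WORtH participant in the pooled percentage. If control attendance is high, the row can look acceptable when adherence to WORtH is not.

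The weight of the control arm also changes with the allocation ratio, so identical WORtH performance can receive different colours for reasons unrelated to the intervention.

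The retention row is not a reliable backstop. Retention counts people with follow-up data, and the Secondary outcomes section says that those who stop the intervention early will still be followed. Someone can abandon WORtH and count as retained.

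**Working it through.** The article gives no arm-level adherence figure, so there is no figure of its own to reproduce. The check asks what WORtH adherence the written rule requires.

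**Inputs from the article.** Cut-offs 65% and 85% (Table 1); 60 recruited (Study population); splits of 30/30 under 1:1 and 40/20 if 2:1 applied to all 60.

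**Assumption.** Control adherence *c* is not given. It is varied from 100% to 80%.

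**Formula.** Pooled adherent count = WORtH adherent + control adherent. With 60 recruited, Green needs 0.85 × 60 = 51 and Amber needs 0.65 × 60 = 39. Hence

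required WORtH adherence = (51 or 39 − *c* × n_control) / n_WORtH.

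| Control adherence | Split | Green needs | Amber needs |
|---|---|---|---|
| 100% | 30/30 | (51−30)/30 = 70% | (39−30)/30 = 30% |
| 100% | 40/20 | (51−20)/40 = 77.5% | (39−20)/40 = 47.5% |
| 90% | 30/30 | (51−27)/30 = 80% | (39−27)/30 = 40% |
| 90% | 40/20 | (51−18)/40 = 82.5% | (39−18)/40 = 52.5% |
| 85% | 30/30 | (51−25.5)/30 = 85% | (39−25.5)/30 = 45% |
| 85% | 40/20 | (51−17)/40 = 85% | (39−17)/40 = 55% |
| 80% | 30/30 | (51−24)/30 = 90% | (39−24)/30 = 50% |
| 80% | 40/20 | (51−16)/40 = 87.5% | (39−16)/40 = 57.5% |

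The 25.5 in the 85% row at 30/30 is the exact product, not a whole count of people.

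**Pattern.** Pooling lowers the WORtH requirement at a cut-off whenever control adherence exceeds that cut-off, and raises it when control adherence is below it. The effect on Green therefore vanishes at 85% and then reverses. The effect on the Amber/Red boundary persists until control adherence falls to 65%.

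**Mixed splits.** The number recruited before suspension is not given. Two illustrations, with 100% control adherence:

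- 42 before (21/21) and 18 after (12/6) gives 33/27. Green needs (51−27)/33 = 24/33 = 73%; Amber needs (39−27)/33 = 12/33 = 36%.
- 30 before (15/15) and 30 after (20/10) gives 35/25. Green needs 26/35 = 74.3%; Amber needs 14/35 = 40%.

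**Same WORtH performance, different colour** (100% control adherence):

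- 70% WORtH adherence: 21 + 30 = 51/60 = 85%, Green at 30/30; 28 + 20 = 48/60 = 80%, Amber at 40/20.
- 40% WORtH adherence: 12 + 30 = 42/60 = 70%, Amber at 30/30; 16 + 20 = 36/60 = 60%, Red at 40/20.

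**Same cut-offs on WORtH alone.** Green needs 26/30 (86.7%) or 34/40 (85%); Amber needs 20/30 (66.7%) or 26/40 (65%).

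**The case against.** The strongest points on the other side are these.

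- **Control adherence is unknown.** The article says only that controls are invited, and its Background lists low energy, amotivation and isolation as barriers in this population. This stands: the 100% figures are a limiting case, and below 85% control adherence the pooled rule is stricter for Green than a WORtH-only rule.
- **A pure 30/30 split is no longer expected.** Recruitment is open at 2:1, so the 70% and 30% figures are a limit and not a forecast. This also stands, apart from chance imbalance from the cluster phase.
- **The WORtH rate will be visible anyway.** Objective i covers adherence in both arms, and the Data analysis wording can be read as WORtH only. Neither changes the rule in Table 1. If the Data analysis wording does mean WORtH only, the two places disagree and need to be aligned.
- **Adherence is not defined in detail, and acceptance of both allocations is a fair feasibility question.** The definition may sit in the full protocol and its absence is no fault here. Adherence across the whole trial can be reported, but as the only adherence element it does not isolate the programme under test.
- **Amber is not a free pass.** It calls for committee discussion, a full review of protocol deviations, solutions to barriers and, if relevant, reconsideration of the intervention. The system guides progression, and even Red is worded as a probable stop. This lowers the severity.

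A reader might infer that the trial as a whole can reach Green with 70% adherence to WORtH. The article does not support that: the worst of four elements decides, so only the adherence element can be said to reach that colour. Nor does it show that 85% was meant for WORtH alone, since the cut-off is stated for the pooled figure.

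**Conclusion.** The point holds for the adherence element of Table 1. As written, the row averages attendance at one session with adherence to a multi-component programme, and its colour moves with control attendance and the allocation ratio.

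The firmer part is the Amber/Red boundary. Across control adherence from 100% down to 80% and splits from 30/30 to 40/20, the row avoids Red with WORtH adherence of between 30% and 57.5%, against 65% if WORtH were judged alone. The effect on Green is conditional: it is material if nearly all controls attend (70–77.5% suffices), small at 90% (80–82.5%), absent at 85% and reversed at 80% (87.5–90%).

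These figures assume 60 recruited and a final split between 1:1 and 2:1; control adherence is an assumption throughout. Severity is moderate: the rule should be corrected while recruitment is open, but review under Amber and the other three elements limit the harm.

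**What to change.** Before results are known:

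1. Reword the Table 1 row to: *% of participants allocated to WORtH who adhere to it*.
2. Keep the 65% and 85% cut-offs, or have the sponsor confirm them for that arm, since they were stated for the pooled figure.
3. Align the Data analysis wording on completing the intervention with the reworded row, so that both name the same arm.
4. Report control session attendance separately, without a threshold.

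The cost is one table row and one sentence. No new data are needed, because objective i already covers adherence in both arms. The row would rest on about 30 to 40 people instead of 60, so each participant shifts it by 1/30 = 3.3 to 1/40 = 2.5 percentage points rather than 1/60 = 1.7. It will usually be harder to meet; the exception is Green when control adherence is below 85%.

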**Retention**			
**% of recruited patients with follow-up data**	< 65%	65–84%	85–100%
**Signal of efficacy**			
**Results for primary clinical outcome and safety**	CI for effect estimate for primary clinical outcome that does not include a clinically important difference or evidence of significant harm	CI for effect estimate for primary outcome that is mostly negative or evidence of potential harm	CI for effect estimate for primary outcome that is mostly positive and no evidence of potential harm

**Green**: progress to main trial with a review of screening logs and protocol to address any barriers to recruitment, adherence or retention.

**Amber**: progress to main trial after discussion with Trial Steering Committee/Trial Management Group with a full review of screening logs and protocol deviations to implement solutions to barriers to recruitment, adherence or retention, and (if relevant) a review of feedback from participants and clinicians, and (if relevant) reconsideration of the intervention.

**Red**: probably not progress to main trial without substantial changes.

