**Methods:**

This 13-week randomised controlled feasibility trial compares the Walking fOR Health (WORtH) multi-component behaviour change intervention, which includes education, goal-setting and self-monitoring, with a one-off education session. It aims to recruit 60 inactive adults with SMI via three community mental health teams in Ireland and Northern Ireland. Primary outcomes are related to feasibility and acceptability, including recruitment, retention and adherence rates, adverse events and qualitative feedback from participants and clinicians. Secondary outcome measures include self-reported and accelerometer-measured physical activity and sedentary behaviour, anthropometry measures, physical function and mental wellbeing. A mixed-methods process evaluation will be undertaken. This study protocol outlines changes to the study in response to the COVID-19 pandemic.

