#### Secondary outcomes

The following outcomes will be measured at baseline and post-intervention, with a subset included at 6, 12, 18 and 24 months follow-up (study objective III) as summarised in Fig. 3:Objective sedentary and physical activity time: All participants will be asked to wear a wrist-worn triaxial accelerometer (Axivity AX3, Open Lab, Newcastle) for at least 4 days. The accelerometer will record how many minutes per day each participant is sedentary and engages in light, moderate and vigorous physical activities. This study will explore the change in average minutes of sedentary behaviour and physical activity before and after the intervention (study objective III).Anthropometric measures: Body mass index will be measured in line with the International Diabetes Federation criteria [33], including height, weight and waist circumference.Self-report of physical activity and sedentary behaviour: The Simple Physical Activity Questionnaire (SIMPAQ) will be used to capture self-reported physical activity [34]. The SIMPAQ includes five items asking about estimated time in bed, structured exercise participation and incidental or non-structured physical activity over the previous 7 days. The Sedentary Behaviour Questionnaire (SBQ) will be used to measure sedentary behaviour and has been shown to have good reliability [35].Mental well-being: Participants will be asked to complete the Warwick-Edinburgh Mental Wellbeing Scale (WEMWBS), a 14-item self-report measure, to assess well-being [36]. Respondents rate their experience regarding each statement over the last 2 weeks. Each item is scored using a 5-point Likert scale ranging from 1 (none of the time) to 5 (all of the time), with the total score ranging from 14 (low well-being) to 70.Functional mobility: Participants will be asked to complete a Timed Up-and-Go (TUG) test [37]. The TUG test requires participants to stand up from a chair, walk 3 m, turn around, walk back and sit down again. The time taken is measured in seconds, and scores represent functional mobility, with higher scores indicating increasing mobility difficulties. Times longer than 13.5 s are predictive of falls in the general older adult population.Motivation to engage in physical activity: Participants will be asked to complete the Behavioural Regulation in Exercise Questionnaire-2 (BREQ-2) which is a 19-item interviewer-administered questionnaire designed to consider an individual’s motivation towards exercise [38]. The BREQ-2 has been validated in people with schizophrenia [39]. They will also be asked to complete the Psychological Needs Satisfaction and Exercise Scale (PNSE), an 18-item questionnaire that measures perceived competence, autonomy and relatedness experienced in exercise contexts [40].

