### Data analysis

Statistical analysis will be performed using SPSS software. The data will be checked for normality, then appropriate descriptive analyses will be used to summarise participant characteristics and outcomes. Feasibility, the primary outcome of this study, will be evaluated by calculating the percentage of people approached who participate in the intervention (recruitment) and the percentage who complete the intervention (retention and adherence).

As this is a feasibility study, significance tests will not be performed on secondary outcomes, such as change in anthropometric measures, physical activity or sedentary time. Intervention effects will be represented by point estimates and their standard deviations. Point estimates will be calculated by subtracting unadjusted mean data at each post-intervention timepoint from the mean data at the baseline timepoint. These will be used along with their standard deviations to estimate a sample size required for a definitive trial, if appropriate [45].

Qualitative data from interviews, dyads and focus groups will be transcribed verbatim, and interpretation, synthesis and data reduction will be undertaken independently by two members of the research team to identify relevant themes. Qualitative findings will be used alongside quantitative outcomes related to process evaluation (BREQ-2 and PNSE) to understand how the intervention was experienced by participants and any changes that they think would improve the intervention.

The traffic light system [46] will be used to guide progression to a main trial, as recommended in recent best practice, and will use the worst performing of the four elements in Table 1 to select which of the following actions to take:

**Table 1 Tab1:** Criteria for progression to main trial

	Red	Amber	Green

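### The signal-of-efficacy row in Table 1 cannot be applied as written: it names no existing outcome, does not match the planned estimates, and its colours overlap

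*Protocol article*

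**What the plan says.** The Abstract states: "Primary outcomes are related to feasibility and acceptability, including recruitment, retention and adherence rates". The Data analysis section agrees, with the words "Feasibility, the primary outcome of this study". Under Secondary outcomes, the list opens with "The following outcomes will be measured at baseline and post-intervention" and covers accelerometry, anthropometry, SIMPAQ, SBQ, WEMWBS, the Timed Up-and-Go test, BREQ-2 and PNSE. None is ranked above the others.

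Table 1 nevertheless has a fourth progression element based on a clinical effect:

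- Red: "CI for effect estimate for primary clinical outcome that does not include a clinically important difference or evidence of significant harm"
- Amber: "CI for effect estimate for primary outcome that is mostly negative or evidence of potential harm"
- Green: "CI for effect estimate for primary outcome that is mostly positive and no evidence of potential harm"

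The four elements are combined by a rule that "will use the worst performing of the four elements in Table 1". For clinical outcomes, the Data analysis section plans point estimates and standard deviations, with the unadjusted post-intervention mean subtracted from the baseline mean. It mentions no confidence interval and describes no comparison between arms.

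**The concern.** The recruitment, adherence and retention rows have numeric cut-offs. The efficacy row depends on an outcome that the article does not have. Read literally, the Amber and Green cells refer to feasibility, which yields percentages and not an effect with an interval. If a clinical measure is meant, the article does not say which one, and the choice could be made once results are known.

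The row also needs an interval that the analysis section does not plan, on an estimate whose sign is not tied to benefit. Finally, the three cells do not divide the possible results into separate classes. Since the worst element sets the action, an indeterminate colour here can leave the progression decision, a main product of a feasibility trial, open to argument.

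**Working it through.** **1. Is there a primary clinical outcome?** The Abstract, the Primary outcome section and Data analysis all make feasibility and acceptability primary. Secondary outcomes names eight instruments or measure groups and singles out none. The Red cell and the row label presuppose a primary clinical outcome, so this is a contradiction within the article.

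As an illustration of the latitude, suppose no true effect and one estimate per listed measure. The chance that at least one of eight favours the intervention is 1 − 0.5⁸ = 0.996 if they are independent, and 1 − 1/9 = 0.89 if they are jointly normal with pairwise correlation 0.5 (assumed). For one outcome named in advance it is 0.50.

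**2. Does the planned estimate fit the row?** The planned estimate is baseline mean minus post-intervention mean. If activity rises, it is negative; if sedentary time falls, it is positive. Both are improvements, so an interval lying mostly above zero has no fixed meaning until direction is set. A within-arm change is also not an intervention effect.

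**3. Are the colours mutually exclusive?** The documents give no figure to reproduce. Inputs:

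- n = 60 (Study population), or 51 = 85% of 60, the Green threshold for retention (Table 1).
- Allocation 1:1 before the suspension and 2:1 after it (Implications of COVID-19 on study delivery).
- Assumed: a between-arm difference in unadjusted means in SD units, normal approximation, 95% two-sided interval, and important difference D from 0.2 to 1.0 SD.

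SE = √(1/n₁ + 1/n₂), and half-width h = 1.96 × SE:

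| Analysed | SE | h (SD) |
|---|---|---|
| 30 / 30 | 0.258 | 0.506 |
| 40 / 20 | 0.274 | 0.537 |
| 51 at 1:1 | 0.280 | 0.549 |
| 34 / 17 | 0.297 | 0.582 |

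Call the estimate e, with positive values favouring the intervention. I read Red as the whole interval lying short of D, that is e + h < D. A symmetric interval lies mostly above zero when e > 0 (Green) and mostly below when e < 0 (Amber).

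*Red with Amber.* When D < h, Red requires e < D − h < 0, so every Red result is also Amber. With no true effect the probability is Φ((D − h)/SE). For 34/17:

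- D = 0.2: Φ(−0.382/0.297) = 0.10
- D = 0.3: Φ(−0.282/0.297) = 0.17
- D = 0.5: Φ(−0.082/0.297) = 0.39

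*Red with Green.* This needs D > h and 0 < e < D − h. With a 95% interval the probability is therefore 0 at D of 0.5 SD or less in all four rows above. For 34/17 with no true effect it is 0.02 at D = 0.6, 0.27 at D = 0.8 and 0.42 at D = 1.0. With an 80% interval (h = 0.38) it is 0.16 at D = 0.5.

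**4. Does the combining rule settle a clash?** It selects the worst of four elements. It does not say which colour one element takes when two of its cells are true.

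**5. How well does the row discriminate?** P(e > 0) = Φ(true effect/SE). For 34/17 this is 0.25 at −0.2 SD, 0.50 at zero and 0.75 at +0.2 SD. These are the most that the Green cell can reach, because it also requires no evidence of potential harm.

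**The case against.** The traffic light only guides progression. Amber still proceeds after committee discussion, and Red means probably not without substantial changes. Since the worst element governs, a flattering choice of outcome cannot rescue poor recruitment, adherence or retention. A sensible committee would probably take the worse of two colours within a row. The article is also a condensed account, and the numerical important difference and interval level may stand in a fuller document. All of this lowers the severity, and the absence of those two numbers is not itself the point. The unnamed outcome, the mismatch with the analysis section and the overlapping cells remain, because they arise from what the article does state.

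Two stronger readings are tempting:

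- **That an ineffective intervention gets a Green decision half the time.** The documents do not support this. The 50% applies to one row, assumes a between-arm contrast and no harm signal, and is a ceiling. Overall Green also needs 100% of the recruitment target and at least 85% adherence and retention. Low discrimination is largely the imprecision of a small feasibility trial, which the article accepts by making no formal sample size calculation.
- **That Red and Green clash at an important difference of 0.5 SD.** With a 95% interval this needs a half-width below 0.5 SD. Baseline adjustment at an assumed correlation of 0.6 would give 0.506 × 0.8 = 0.41 at 30/30, but the article specifies unadjusted means. A between-arm difference in change scores at the same assumed correlation would multiply h by √(2 × 0.4) = 0.894, giving 0.45 (30/30) to 0.52 (34/17). The clash is therefore conceivable under some choices but does not follow from the plan. Clustering among participants recruited before the suspension would widen the interval and make it rarer.

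**Conclusion.** The point holds. The efficacy row gives no determinate colour: it refers to a primary clinical outcome that does not exist, asks for an interval on an effect that the analysis section does not plan, leaves direction open, and has cells that can be true together. Red/Amber is the more frequent overlap for important differences up to 0.5 SD: about 0.10 to 0.39 over 0.2 to 0.5 SD, with no true effect and 51 analysed at 2:1. Red/Green is possible in logic but, on unadjusted means with a 95% interval, needs a difference above about 0.51 to 0.58 SD.

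These sizes rest on an assumed between-arm contrast, interval level and range of D. The contradiction over the outcome rests on none of them. A reader might conclude that the whole progression decision is unreliable; that goes too far, because the other three rows have numeric thresholds and this row can only pull the result down. It should be fixed, but it does not undermine the trial.

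**What to change.** Before any outcome data are analysed:

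1. Name in Table 1 one clinical outcome and timepoint that both phases collect, for example a single accelerometer measure at 13 weeks. State its direction of benefit, the between-arm estimate, the interval level and the important difference, or refer to the document that fixes them. Use the same term in all three cells.
2. Align the Data analysis section, so that it plans this between-arm estimate with its interval and a sign convention.
3. Apply the cells in order. Red if the interval limit in the direction of benefit falls short of the important difference, or there is evidence of significant harm. Otherwise Amber if the estimate does not favour the intervention, or there is evidence of potential harm. Otherwise Green.
4. State that Green on this row is not evidence of efficacy. With no true effect and no harm signal, up to about 50% of trials would be Green on this row alone. Ordering the cells does not change that when the important difference is below the half-width; above it, for 34/17, the figure falls to 0.48, 0.23 and 0.08 at D = 0.6, 0.8 and 1.0 SD.

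The cost is rewording one table row and a few sentences of Data analysis while the trial is still recruiting. The small downside is that the sponsor must commit now to one outcome and one difference.
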